24 genetically LP subjects with no GI symptoms in response to the ingestion of lactose (group 1).24 genetically lactase-non-persistent (LNP) subjects with no GI symptoms in response to the ingestion of lactose (group 2).72 genetically LNP subjects with GI symptoms in response to lactose ingestion (group 3).

Participants confirmed as genetically LP but experiencing GI symptoms after ingesting lactose will be excluded, as factors other than primary hypolactasia likely explain their symptoms.

The groups are chosen to allow discrimination of metabolic signals that relate to the genetic and clinical phenotypes of LI. Group 3 intentionally comprises more individuals to allow for secondary analysis of the differences in symptom severity, which is often very variable. The groups are important to enable the detection of biomarkers sensitive to differences in symptoms of LI to be captured.

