**Figure 2 F2:**
[figure not shown]
Overview of the planned intervention sampling protocol at the study site. EBC, exhaled breath condensate.

The urine samples will be used for metabolomics analysis and, in the case of female participants, for a pregnancy test. Participants with a positive pregnancy test will be excluded.

All measures are indicated with respect to the start of the test (ie, the start of the consumption of the assigned carbohydrate solution), defined as t_0_.

In addition, the participants will fill out the questionnaire on LI (as used for the screening survey) at time −30 and −10 min to describe symptoms of LI before the test (baseline symptoms).

Thirty minutes before the start of the test, participants will be instructed to affix two DigeHealth wearable devices around their abdomen to record bowel sounds: one in the upper left abdominal region and another in the lower right abdominal region.

The participants will be assigned to one of the two carbohydrate challenges using stratified randomisation based on the three groups defined by the pre-screening tests. The randomisation is defined using a web-based randomisation procedure, the Clinical Trial Randomization Tool provided by the National Cancer Institute’s Division of Cancer Prevention (https://ctrandomization.cancer.gov). 100 participants will be assigned to the lactose group and asked to ingest 25 g of lactose dissolved in 150 mL of water. The remaining 20 participants (4 participants from each group 1 and 2, and 12 participants from group 3) will be assigned to the glucose group and asked to ingest equimolar amounts of glucose (13 g)^83^ dissolved in 150 mL of water. The participants and investigators will be blinded during testing to the type of carbohydrate solution assigned. Measurement bias will be addressed for all analytical platforms by measuring the samples without removing the blinding.

For each participant, the carbohydrate solution must be consumed in a time lapse of 5 min. Following the solution intake, participants will be asked to rinse their mouths with a standard quantity of water (500 mL) to avoid the detection of solution-relevant residual molecules in the oral cavity.

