### Statistical analysis

#### Primary endpoint

Supervised machine learning algorithms (such as random forest and partial least squares discriminant analysis) will be applied based on Zheng *et al*^100^ and will identify molecular breath profiles that discriminate different clinical traits associated with LM based on the levels of metabolites in the exhaled breath after the intake of lactose. Models will be created to explore separately the breath profiles that are discriminated for each trait of LM, including the response to the LHBT, polymorphisms for LP, lactose-derived metabolites in urine and the GI symptoms of LI taken individually and collectively. To reduce overfitting and deliver reliable estimates of the models, we will apply machine learning with voting, a strategy for classification based on selecting the output with the most classes. Clinical traits will be modelled as either categorical variables, continuous variables or both, where appropriate. This analysis will be conducted first on a subset of 50% of the recruited participants to allow the most predictive metabolites to be identified within the timeframe of the study. The subset will be balanced to represent the three test groups. The same analysis workflow will later be applied to the whole cohort, with 20 participants (stratified for group) removed from all modelling to allow for internal validation of the models. The best profiles (Lactobreath profiles) that associate the breath exhalome with each of the clinical traits of LM will be tested in the 20 remaining participants to assess their validity. Further, to consider the specificity of the Lactobreath profiles for lactose metabolism, the profiles will be evaluated in the participants assigned to the glucose test with additional comparisons between intervention types (glucose vs lactose) across all three participant groups. The molecular profiles with the best performance for predicting LM clinical traits will be retained to determine the identity and quantification of the molecules composing the selected profiles.

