The diagnostic performance of the lactose-induced breath profiles identified for the clinical traits will be assessed using the following parameters: sensitivity, specificity, positive predictive value, negative predictive value, the likelihood ratio of a positive test, likelihood ratio of a negative test as described by Beyerlein *et al*^17^ and Jellema *et al*.^81^ For each parameter, the novel breath profiles will be compared with the reference diagnostic tool. The participants are grouped by LHBT and genetic test results as these are commonly used in clinical practice for LI diagnosis and are, therefore, suitable for evaluating the performance of the breath biomarkers. The level of significance will be two-sided (α=0.05). Corrections for multiple testing will be made using the false discovery rate.^101^

Analysis populations: the analysis populations are defined by the criteria used to select the three study groups and the two assigned carbohydrate interventions, resulting in six groups for analysis.

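### An unweighted majority vote on a lactose arm recruited 20:80 by genotype and 40:60 by screening symptoms shifts the diagnostic operating point towards the larger class, and every listed performance measure depends on that point

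*Protocol article*

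**What the plan says.** Study population and eligibility sets quotas of 24, 24 and 72 for the three groups: lactase-persistent (LP) without symptoms, lactase-non-persistent (LNP) without symptoms, and LNP with symptoms. It gives the reason for the imbalance: "Group 3 intentionally comprises more individuals to allow for secondary analysis of the differences in symptom severity".

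Intervention day fixes the allocation. It says "100 participants will be assigned to the lactose group", and that the glucose arm takes "4 participants from each group 1 and 2, and 12 participants from group 3".

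The primary-endpoint text of the statistical analysis names random forest and PLS-DA as examples of the classifiers. Each clinical trait is modelled separately, including LP polymorphisms and gastrointestinal symptoms. To limit overfitting, the section adopts voting, described as "a strategy for classification based on selecting the output with the most classes". Twenty participants, stratified by group, are kept out of the modelling for internal validation.

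The same section measures diagnostic performance by sensitivity, specificity, the two predictive values and the two likelihood ratios, and adds: "For each parameter, the novel breath profiles will be compared with the reference diagnostic tool". The Outcomes section makes this diagnostic performance the primary endpoint and presents it as a benchmark against current practice.

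**The concern.** An unweighted vote has an implicit cut-off at half the votes. Where that cut-off falls on the underlying score depends on the class mix of the training data. Here the mix is a recruitment quota, enlarged in group 3 for a secondary severity analysis. It represents neither a prevalence nor a chosen balance between false positives and false negatives.

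The primary endpoint would then report sensitivity and specificity at a point that nobody chose. A reference test with its own threshold would be compared with a profile whose threshold was set by the quotas. A profile that separates the classes well could show poor specificity, and the measures listed would not say whether the profile or the cut-off was to blame.

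**Working it through.** **1. Class mix, from the plan's own figures.** Lactose arm = (24 − 4) + (24 − 4) + (72 − 12) = 20 + 20 + 60 = 100, which agrees with the stated 100.

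- Genotype, LP:LNP = 20 : (20 + 60) = 20:80.
- Screening symptoms, absent:present = (20 + 20) : 60 = 40:60.

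If the 20 validation participants come from the lactose arm in proportion (4/4/12, an assumption), modelling uses 16/16/48 = 80 people. That is 16:64 for genotype and 32:48 for symptoms. LNP and symptoms present are taken as the positive classes.

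**2. Closed form for one well-calibrated score.** Assume an equal-variance binormal score, cut where the posterior probability is 0.5 under the sample mix. Then d = √2·z(AUC), sensitivity = Φ(d/2 + ln(odds)/d) and specificity = Φ(d/2 − ln(odds)/d). A balanced cut gives Φ(d/2) for both.

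For AUC 0.90, d = 1.414 × 1.2816 = 1.812 and d/2 = 0.906.

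- Genotype, odds 4: ln 4/d = 1.386/1.812 = 0.765. Sensitivity = Φ(1.671) = 0.95 and specificity = Φ(0.141) = 0.56.
- Symptoms, odds 1.5: ln 1.5/d = 0.405/1.812 = 0.224. Sensitivity = Φ(1.130) = 0.87 and specificity = Φ(0.682) = 0.75.
- Balanced cut: Φ(0.906) = 0.82.

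At AUC 0.80 the specificities are 0.28 (genotype), 0.60 (symptoms) and 0.72 (balanced).

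**3. Simulation of a voting forest.** The document gives no effect sizes, so these are assumptions: 300 trees, independent Gaussian features (1000, 200 or 50, of which 20, 10 or 5 are informative), 80 training cases, 500 new test cases per class and 15 repeats. The alternative cut-off is taken from out-of-bag scores where sensitivity and specificity are about equal. Entries are sensitivity/specificity.

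| Training mix | Features | AUC | 50% vote | Out-of-bag cut |
|---|---|---|---|---|
| Genotype 16:64 | 1000 | 0.76 | 1.00/0.00 | 0.66/0.71 |
| Genotype 16:64 | 1000 | 0.90 | 1.00/0.00 | 0.76/0.85 |
| Genotype 16:64 | 200 | 0.89 | 1.00/0.01 | 0.77/0.83 |
| Genotype 16:64 | 50 | 0.91 | 1.00/0.19 | 0.82/0.83 |
| Symptoms 32:48 | 1000 | 0.86 | 1.00/0.13 | 0.77/0.79 |
| Symptoms 32:48 | 1000 | 0.96 | 1.00/0.33 | 0.85/0.91 |
| Symptoms 32:48 | 50 | 0.94 | 0.95/0.71 | 0.85/0.87 |
| Equal 40:40 | 1000 | 0.87 | 0.80/0.76 | 0.76/0.79 |
| Equal 40:40 | 1000 | 0.96 | 0.89/0.89 | 0.88/0.90 |

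With equal classes the plain vote is already close to balanced, so the loss comes from the class mix.

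**4. Dependence on the algorithm.** In a companion run (12 repeats), two-component PLS-DA cut at 0.5 gave these genotype results: 1.00/0.06 at AUC 0.88 (1000 features), 0.96/0.45 at AUC 0.87 (200) and 0.94/0.58 at AUC 0.90 (50). A forest restricted to the best 10 or 20 of 1000 features, selected in training, gave genotype specificity 0.42 and 0.33 at AUC 0.92 and 0.95. Its symptom specificity was 0.80 and 0.84 at AUC 0.96 and 0.97.

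**5. What rebalancing alone achieves.** Drawing equal numbers per class for each tree, while keeping the 50% vote, gave genotype specificity 0.19 at AUC 0.90 with 1000 features and 0.63 at AUC 0.92 with 50. In high dimension this corrects only part of the shift.

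**The case against.** The strongest reply is that the faulty rule is inferred. The article never says that votes are unweighted or cut at 50%. Its sentence on voting is garbled, and the stated purpose, less overfitting, would also fit a vote across resamples or models. The algorithms are only examples, based on a cited method. Weights or thresholds could sit in that method or in an analysis plan that is not shown. This stands as a limit on certainty. It does not remove the point, which rests on three things that the article does state: a most-votes rule, a quota-fixed mix, and a list of measures that all depend on the cut-off. A vote across models inherits whatever cut-off each model uses. The only wording about balance concerns the interim 50% subset, and it does not say whether equal or proportional numbers are meant.

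The second reply is that a degenerate classifier would be noticed. This is correct. The forest result 1.00/0.00 has a positive likelihood ratio of 1.00/(1 − 0.00) = 1.0, visibly uninformative. At the out-of-bag cut the same scores give 0.76/(1 − 0.85) = 5.1. The likelihood ratios would expose the failure, but they would not show that a different cut-off repairs it.

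The third reply concerns reach. The 40:60 split describes symptoms at home screening; test-day or single symptoms may split differently. Breath-hydrogen response and urinary metabolites have no designed mix, and traits modelled as continuous involve no class vote. All of this stands.

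**Conclusion.** The point holds for the categorical genotype and screening-symptom models. Taken as an unweighted vote, the stated rule lets the recruitment mix pull the operating point towards high sensitivity and low specificity. At AUC about 0.9, genotype specificity is about 0.00 to 0.58 depending on algorithm and number of features, against about 0.82 to 0.85 at a balanced cut-off. For symptoms the loss is usually smaller. The direction follows from the stated mix. The size rests on assumed independent Gaussian features and assumed effect sizes.

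Four stronger readings are not supported:

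- **Genotype specificity will be near zero.** That arises with an unweighted forest on many features. The pilot cited in the power section detected thousands, which makes the case relevant, but the article fixes neither the algorithm nor the feature set.
- **The reported values would be wrong.** They are valid for the rule used; the fault is a poorly placed operating point.
- **All traits are affected.** Only genotype and screening symptoms have a mix fixed by design.
- **Every comparison is against the breath-hydrogen test at its fixed 20 ppm threshold.** The article names only a reference diagnostic tool, so the comparison reflects the recruitment mix in part and to an unknown degree.

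**What to change.** In the primary-endpoint analysis, replace the plain vote for categorical traits with class-weighted (prior-adjusted) votes, or with a class-balanced cut-off chosen on out-of-bag or inner-fold votes. Set it within the training data and carry it unchanged to the 20 validation participants. The out-of-bag or inner-fold cut-off is the safer choice, because equal-class resampling alone left much of the shift in the high-dimensional runs. If weighting is used, check on out-of-bag votes that sensitivity and specificity are roughly balanced.

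In the list of performance measures, add the AUC with a 95% interval for each categorical trait. Comparison with the reference tool at matched specificity is optional.

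The cost is some analysis code and a few sentences of text, with no further participants or measurements. Raw accuracy and headline sensitivity will be less favourable. The change does not cure small numbers: a proportional validation set holds about 4 LP participants, and even 4 of 4 correct has an exact 95% lower limit of 0.025^(1/4) = 0.40 for genotype specificity.

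### The final breath profiles get their only independent test among lactose takers in 20 people, the set used for the accuracy measures is not named, and the 20 are not said to be separate from the 50% discovery subset

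*Protocol article*

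**What the plan says.** All references are to the protocol article.

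- **Outcomes, Primary endpoints:** the primary endpoint is how well the breath profiles discriminate the clinical traits of lactose malabsorption. The stated reason is to benchmark the new test against current practice.
- **Statistical analysis, Primary endpoint, stage 1:** "This analysis will be conducted first on a subset of 50% of the recruited participants to allow the most predictive metabolites to be identified". The subset is balanced over the three groups.
- **Same section, stage 2:** the same workflow is later applied to the whole cohort, "with 20 participants (stratified for group) removed from all modelling to allow for internal validation of the models". The best profile for each trait is tested in those 20.
- **Same section, afterwards:** "The molecular profiles with the best performance for predicting LM clinical traits will be retained", so that their molecules can be identified and quantified.
- **Same section, performance measures:** sensitivity, specificity, positive and negative predictive value and both likelihood ratios. "For each parameter, the novel breath profiles will be compared with the reference diagnostic tool". The level is two-sided 0.05 with false discovery rate correction. The evaluation set is not named.
- **Study population and eligibility; Intervention day:** the groups have 24, 24 and 72 members. "100 participants will be assigned to the lactose group", and 20 (4, 4 and 12) receive glucose.

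**The concern.** A primary endpoint of diagnostic performance has to be estimated on people who did not help to build the profile, and on enough of them to be informative. The only such lactose takers in the plan are the 20. The glucose participants serve a different purpose, the specificity of the profiles to lactose.

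Two questions follow. First, can 20 people support six accuracy measures and a significance comparison with the reference tool? Second, are the 20 untouched? They first appear with the later whole-cohort run, after predictive metabolites have been identified in half of the participants. The plan does not say when the 20 are drawn or that they lie outside that half. At stake is whether the reported accuracy can be interpreted and whether the benchmark against current practice can be delivered.

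**Working it through.** **1. Counts.** The lactose arm is (24−4) + (24−4) + (72−12) = 20 + 20 + 60 = 100, and 100 + 20 = 120. This reproduces the plan's allocation. The plan states no power, precision target or expected accuracy for the hold-out, so there is no such figure to reproduce.

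**2. Composition of the hold-out.** The plan does not give the split. Proportional stratification gives 20 × (20, 20, 60)/100 = 4, 4, 12. Starting from 24/24/72 gives the same. If test-day status follows the screening groups, there are 12 people with symptoms and 8 without, or 4 lactase-persistent and 16 non-persistent.

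**3. Precision in the 20.** Exact (Clopper–Pearson) 95% limits for x successes in n are the 0.025 quantile of Beta(x, n−x+1) and the 0.975 quantile of Beta(x+1, n−x). The success counts are assumed, since the plan gives none.

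| Measure | Result | 95% interval |
|---|---|---|
| Symptom sensitivity | 10/12 = 83% | 52–98% |
| Symptom specificity | 7/8 = 88% | 47–99.7% |
| Lactase-persistent correctly classified | 4/4 = 100% | 40–100% |
| Perfect sensitivity | 12/12 | 74–100% |
| Perfect specificity | 8/8 | 63–100% |

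The positive likelihood ratio is (10/12)/(1/8) = 6.7. The standard error of its logarithm is √(1/10 − 1/12 + 1/1 − 1/8) = 0.94, so the 95% interval is 1.05 to 42.

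**4. Comparison with the reference tool.** The plan names no test. Taking an exact McNemar test for sensitivity or specificity, k discordant pairs all in one direction give p = 2 × 0.5^k:

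- k = 4: 0.125
- k = 5: 0.0625
- k = 6: 0.031

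At least six one-way discordant pairs are therefore needed, before any false discovery rate correction. That is a difference of 6/12 = 50 percentage points among 12 people, or 6/8 = 75 points among 8. Among 4 people significance cannot be reached.

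**5. Same kind of estimate over all 100 lactose participants, out of fold.** At an assumed 85%, sensitivity 51/60 has 73–93% and specificity 34/40 has 70–94%. These intervals are approximate because cross-validated predictions are not independent.

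**6. Overlap with the 50% subset.** Suppose 50 of the 100 lactose participants (10/10/30) form the subset and the 20 are drawn without regard to it. The expected overlap is 10. The chance of none is [C(10,4)/C(20,4)]² × C(30,12)/C(60,12) = 1.2 × 10⁻⁷. Equally, 50 people remain outside the subset, so a disjoint 20 is easy to arrange.

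**7. What overlap would do (hypothetical).** Pure noise was simulated with 2,000 features, 60 against 40 people, the top 20 features kept, and 600 runs. The true AUC is 0.50.

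| Scenario | Mean AUC in the 20 |
|---|---|
| Overlapping 20, stage-1 features carried forward | about 0.80 |
| Overlapping 20, features re-selected without them | about 0.50 |
| Disjoint 20 | about 0.50 |

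**The case against.** The strongest reply concerns bias. A reader might infer that the 20 leak into discovery, so that the reported performance is inflated. The documents do not support that as a statement of fact. The plan removes the 20 from all modelling, which read plainly covers stage 1 too. It also applies the same workflow again to the whole cohort, which suggests that features are re-selected. Under either reading the simulated bias disappears. The 1.2 × 10⁻⁷ figure assumes a draw made without regard to the subset, and the plan describes no such draw.

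A reader might also infer that the final profiles are chosen on their hold-out results. The sentence on retaining the best performers concerns which profiles go on to chemical identification, and the best profiles are named before they are tested in the 20. Choosing on the hold-out is possible but not stated.

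Other parts of the reply also stand. A reserved hold-out is a recognised form of internal validation. The plan does not say that the 20 are the only basis for the accuracy measures. Symptoms are measured again on the test day, so 12 against 8 is an approximation. Some traits may be modelled as continuous. The study is a pilot and proof of concept, and the Discussion says that a second study must confirm reproducibility in other populations.

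None of this removes the imprecision. Nor can the point simply be deferred to a fuller document, because the article itself fixes the hold-out size, the order of the stages, the six measures and the significance level. Its sample-size rationale concerns discovering metabolites that respond to an intervention, not estimating accuracy.

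**Conclusion.** The point holds in two parts of different strength.

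**Firm.** Whichever set is meant, the primary performance estimate has a problem. On the 20 alone, intervals run from about one half to nearly 100% for sensitivity and specificity, and from 40% for the lactase-persistent group. The reference comparison could then succeed only with a very large difference. On a set that includes training data, the estimates are optimistic. Voting among models may reduce overfitting, but it does not by itself give an unbiased performance estimate. This part rests on proportional stratification and on assumed accuracies of about 83–100%. Even perfect results leave lower limits of 74% (12/12) and 63% (8/8).

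**Conditional.** Upward bias arises only if the 20 overlap the 50% subset and stage-1 selections are carried into the final profiles. The plan leaves both open, and its wording leans against them. The AUC of 0.80 shows how large the effect could be under an assumed procedure. It is not a forecast for this trial.

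Given the pilot status and the further study the authors say is needed, this should be corrected but falls below a must-fix.

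**What to change.** 1. Name the set on which the six accuracy measures and the reference comparison are computed.
2. Make the primary performance estimate repeated stratified nested cross-validation over the 100 lactose participants. Keep all feature selection, tuning, voting and choice of profile inside the training folds. Report confidence intervals and note that they are approximate.
3. If the 20 are kept as a check, draw them before the 50% analysis, state that they are excluded from it, and use them once after the profiles are locked. Make no significance claim against the reference tool from these 20 alone.

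The cost is computing time and a few sentences, with no extra participants. Reported performance may be lower than under the present wording. The hold-out must be fixed before the 50% analysis is run.

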### Genetic and lactose tolerance screening

For all eligible participants, a home screening test will be conducted after consent is obtained. The home screening test kit will contain lactose powder and accompanying information so that the subjects can conduct a lactose tolerance test (according to the LHBT protocol) at their home. The test will be conducted based on a standardised, previously validated questionnaire,^17^ adapted to the most recent guidelines (https://www.esnm.eu/guidelines.html)^80^,^82^ that propose the use of 25 g of lactose for lactose tolerance testing. Briefly, abdominal pain, nausea, bloating, diarrhoea, borborygmi, as well as the sum of all symptoms, will be measured on a 10-point scale with symptom intensities ranging between 0 and 9. The home screening test kit will also provide material to collect a buccal sample to determine genetic polymorphisms commonly modulating LP.

From the participants who return the buccal samples and whose polymorphism for LP is measured, 120 participants will be selected and distributed into three groups based on their LP genetic profiles and symptomatic response to the ingestion of 25 g of lactose (lactose solution).

LP volunteers experiencing symptoms will be excluded as factors other than primary hypolactasia likely explain their symptoms.

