### Outcomes

#### Primary endpoints

The primary endpoint is the diagnostic performance of the Lactobreath profiles (the molecular breath profiles) for discriminating different clinical traits associated with LM after lactose intake. The choice of this endpoint allows an objective comparison with the current diagnostic measures used for LI diagnosis. It thus allows the novel test to be benchmarked against the current practice.

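### PPV and NPV are primary-endpoint measures in a sample whose composition is set by quota, so raw values reflect the quotas as well as the test and do not carry over to practice

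*Protocol article*

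**What the plan says.** Under Outcomes, Primary endpoints, the protocol article makes the diagnostic performance of the breath profiles the primary endpoint and says of this choice: "It thus allows the novel test to be benchmarked against the current practice". Under Statistical analysis, Primary endpoint, performance is to be measured by "sensitivity, specificity, positive predictive value, negative predictive value, the likelihood ratio of a positive test" and the likelihood ratio of a negative test. The same paragraph has each of these compared with the reference diagnostic tool, and names the hydrogen breath test (LHBT) and the genetic test as the tools in common clinical use.

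Study population and eligibility fixes who is in the sample:

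- "24 genetically LP subjects with no GI symptoms in response to the ingestion of lactose (group 1"
- "24 genetically lactase-non-persistent (LNP) subjects with no GI symptoms in response to the ingestion of lactose (group 2"
- "72 genetically LNP subjects with GI symptoms in response to lactose ingestion (group 3"

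The fourth combination is removed: "Participants confirmed as genetically LP but experiencing GI symptoms after ingesting lactose will be excluded". The imbalance is deliberate: "Group 3 intentionally comprises more individuals to allow for secondary analysis of the differences in symptom severity". Genetic and lactose tolerance screening confirms that "120 participants will be selected and distributed into three groups based on their LP genetic profiles and symptomatic response".

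The article does not say at what prevalence PPV and NPV are to be stated, does not weight them back to the screened pool, and does not call them conditional on the group sizes.

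**The concern.** Predictive values depend on the share of the sample that has the trait. In this study that share was chosen for other reasons, chiefly to study symptom severity within group 3. A PPV or NPV counted directly from these participants answers a question about the 24/24/72 mix and not about people who would take the test. Because the measures belong to the primary endpoint and are meant to be set against current practice, a reader is likely to take a high PPV as clinical performance.

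The benchmark has a related weakness. Genotype and screening symptoms were both used to select participants, and one cell of their cross-table was emptied. If the genetic test is used as comparator for screening-defined symptoms, its accuracy is already determined before any breath is measured.

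**Working it through.** **Inputs from the article.** Groups 24, 24 and 72 (Study population and eligibility). Glucose allocation 4, 4 and 12 (Intervention day). A validation set of 20, stratified for group (Statistical analysis, Primary endpoint). About one-third of people worldwide keep lactase activity as adults (Introduction), hence about two-thirds LNP.

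**Assumed, because the article gives no value.** Sensitivity (Se) = specificity (Sp) = 85%, and symptom prevalences of 10% to 30% among test users.

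**Sample composition.** 24 + 24 + 72 = 120, as stated. The lactose arm is 24 − 4 = 20, 24 − 4 = 20 and 72 − 12 = 60, total 100, as stated.

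- Symptomatic at screening: 72/120 = 60%; lactose arm 60/100 = 60%.
- LNP: (24 + 72)/120 = 80%; lactose arm (20 + 60)/100 = 80%.
- A validation set drawn proportionally from the lactose arm would be 4/4/12, with the same shares.

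**Predictive values at prevalence p.**

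PPV = Se·p / [Se·p + (1 − Sp)(1 − p)]

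NPV = Sp(1 − p) / [Sp(1 − p) + (1 − Se)p]

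| Trait | p | PPV | NPV |
|---|---|---|---|
| Symptoms, quota | 60% | 0.51/0.57 = 89% | 0.34/0.43 = 79% |
| Symptoms, assumed | 30% | 0.255/0.36 = 71% | 0.595/0.64 = 93% |
| Symptoms, assumed | 20% | 0.17/0.29 = 59% | 0.68/0.71 = 96% |
| Symptoms, assumed | 10% | 0.085/0.22 = 39% | 0.765/0.78 = 98% |
| LNP, quota | 80% | 0.68/0.71 = 96% | 0.17/0.29 = 59% |
| LNP, Introduction | 2/3 | 0.567/0.617 = 92% | 0.283/0.383 = 74% |

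The likelihood ratios are 0.85/0.15 = 5.7 and 0.15/0.85 = 0.18 in every row. As a reference point, a test with no information (Se = Sp = 50%) has PPV = p, so it would show a PPV of 60% for symptoms and 80% for LNP from the quotas alone.

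**Genetic test as comparator for screening symptoms** (LNP = positive). Se = 72/72 = 100%; Sp = 24/48 = 50%; PPV = 72/96 = 75%; NPV = 24/24 = 100%. The lactose arm gives the same values: 60/60, 20/40, 60/80 and 20/20. All four follow from selection.

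Suppose instead that a fraction f of LP volunteers had symptoms and were kept in proportion. That adds 24f/(1 − f) people. For f = 10% to 30% (assumed) this is 2.7 to 10.3 people. Se becomes 72/74.7 = 96% to 72/82.3 = 88% (87.5% before rounding), and NPV becomes 24/26.7 = 90% to 24/34.3 = 70%.

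**Specificity is affected too.** Specificity for symptoms pools groups 1 and 2, which are equal in size by design: Sp = ½·Sp(LP) + ½·Sp(LNP). If the breath profile behaves differently in the two groups, the pooled figure also depends on the quota, and Bayes' rule applied to it would carry that forward.

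**The case against.** The strongest reply has five parts.

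- **Prevalence-free measures are already planned.** Sensitivity, specificity and both likelihood ratios are on the list, and a reader can convert the ratios to predictive values at any prevalence. This stands, and it keeps the matter from being critical.
- **The study is a pilot and proof of concept.** The Discussion asks for confirmation in other populations and in patients with other gastrointestinal disorders. This is partial mitigation only, since it says nothing about PPV or NPV, while Primary endpoints still speaks of benchmarking against practice.
- **Breath and reference tests are compared in the same people.** Both face one prevalence, so the quotas do not by themselves favour either. This stands. The difficulty lies in the absolute values and in the genotype benchmark for screening symptoms.
- **A separate analysis plan may set the prevalence.** That is possible, but the article itself fixes PPV, NPV and their comparison with the reference without any such condition.
- **The lower symptom prevalences are assumptions.** This is true. At the only population figure the article gives, genotype PPV moves just from 96% to 92%. NPV rises from 59% to 74%, so the quota understates the test there.

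Three stronger readings are tempting, and the article does not support them. A reader might infer that PPV and NPV reflect the quotas *instead of* the test; they also depend on sensitivity and specificity. A reader might take 60% as the prevalence of every symptom outcome analysed. It is the share at home screening; symptoms are recorded again on the test day, and those results and LHBT positivity are shaped by the quotas but not fixed by them. A reader might conclude that comparison with the genetic test is empty throughout. The predetermined 100/50/75/100 figures hold only for screening-defined symptoms, and the article does not say that the genetic test will be the comparator for that trait.

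**Conclusion.** The concern holds in a limited form. Raw PPV and NPV from this sample are tied to a 60% symptomatic share at screening and an 80% LNP share, both chosen by design, and should not be read as performance in practice.

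Under the 85% accuracy assumption, the quota raises symptom PPV by 18 percentage points against a 30% prevalence (89% versus 71%) and by 50 or 51 against 10% (89% versus 39%; 50.8 before rounding). It lowers NPV by 14 and 19 points respectively. For genotype against the article's own two-thirds figure, the shifts are 4 points up in PPV and 15 points down in NPV. These sizes depend on the assumed accuracy and, for symptoms, on assumed prevalences. The direction does not: for an informative test with fixed sensitivity and specificity, a higher prevalence raises PPV and lowers NPV.

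This should be fixed before the analysis. It does not invalidate the primary endpoint.

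**What to change.** 1. Make sensitivity, specificity and the likelihood ratios the lead measures. Report specificity for symptoms separately in group 1 (LP) and group 2 (LNP).
2. Give PPV and NPV only by Bayes' rule over a stated prevalence range, such as 10% to 60%, with the LP:LNP mix among people without symptoms also stated. Alternatively, reweight to the genotype-by-symptom frequencies of the screened pool, which the home kit yields. With pool shares w1, w2 and w3 for the three groups, PPV = Se·w3 / [Se·w3 + (1 − Sp1)w1 + (1 − Sp2)w2], and NPV = (Sp1·w1 + Sp2·w2) / [Sp1·w1 + Sp2·w2 + (1 − Se)w3].
3. State how LP volunteers with symptoms are handled. Their breath is never measured, so either limit the target population to the three enrolled cells or add the fourth cell with a stated range for its sensitivity.
4. Label any raw PPV or NPV as conditional on the quotas.
5. Do not use the genetic test as comparator for screening-defined symptoms.

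No new participants or measurements are needed. The costs are slightly more analysis, a less favourable PPV, and less precise specificities: 20 people per group in the lactose arm, and 4 per group in a proportional validation set. The screened pool consists of volunteers recruited by advert, so reweighted values should be described as applying to that pool and not to patients in practice.
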